**Improbable:**

- A clinical event, including anomalous laboratory test findings, with a time relation to administration of the drug which makes a causal association unlikely, and where other drugs, chemical substances or intercurrent disease afford plausible explanations for the observed event.

**Unrelated:**

- None of the above criteria are met.

## 9.3. PROCEDURE FOR REPORTING ADVERSE EVENTS

**The investigator:**

The investigator will immediately notify the study sponsor of any serious and/or unexpected adverse events (see section 9.1.).

The report will be realized during the first 24 hours since the start of the serious adverse event. Notification will be made by means of the adverse events reporting form contained in Appendix V of this protocol. This form will be sent to the sponsor by fax.

Adverse events identified in the course of a clinical trial are to be documented in the database (see Appendix I for CRD content).

All adverse events will be notified in table form in the final report of the clinical trial.

All adverse events will be recorded, regardless of the imputability (i.e., causal) relationship involved, in the corresponding adverse events description form. The latter is found in the CRF of each participant in the study (see Annex I).

Depending on the nature of the condition, each adverse event is to be classified as:

- serious / not serious
- unexpected / expected

The characteristics of the event, its seriousness and "expectability", determine when and how it is to be reported to the health authorities.

The recording of adverse events is the responsibility of the trial investigator team, which should indicate the time of appearance of the event (expressed in the shortest time unit possible), its serious / not serious status, and whether it was expected or unexpected. The intensity of the event (mild, moderate or severe) is to be specified, along with the measures adopted (none, treatment, exclusion), course (complete remission, partial remission, persistence) and imputability based on the criteria indicated in section 9.2.

Intensity will be assessed by the investigator using the following terms according to the OMS criteria:

- Grade I-II
- Grade III-IV

**The sponsor:**

The sponsor will inform the Spanish Drug Agency (Ministry of Health), the competent authorities of the autonomous region and the Ethics Committees implicated in the clinical trial about any important information of security of the investigational medicinal product.

The sponsor will inform the Spanish Drug Agency (Ministry of Health) of any serious and unexpected adverse events which may be related to the study treatment, when the investigational medicinal product is not marketed. When it is marketed, it will be informed by means of requirements of pharmacovigilance.

The sponsor will inform competent authorities of the implicated autonomous region and the Ethics Committee of any serious and unexpected adverse events which may be related to the study treatment, and that have been happened in patients in its autonomous region.

The deadlines to notify suspect adverse reaction are:

- 15 days
- 7 days if the suspect adverse reaction has resolved in death or has been life-threatening. The information will be completed in 8 further days.

If the notification is sent in electronic form, it is not necessary to notify the competent authorities of the autonomous region.

The sponsor will keep a detailed register of all the adverse events notified by the investigators.

# 10.- ETHICAL ASPECTS

## 10.1. GENERAL CONSIDERATIONS

### 10.1.1. Declaration of Helsinki

The trial will be conduction in compliance with the principles of the last version of the Declaration of Helsinki

### 10.1.2. Ethics Committees and Regulatory Authority

The present study will be carried out in accordance with Spanish legislation, and the documentation required prior to initiation of the trial is the following:

- Protocol acceptance by the sponsor and the principal investigator
- Protocol approval by the Ethics Committee.
- Protocol authorization from the Spanish Drug Agency (Ministry of Health)

All subjects will be guaranteed continued medical and nursing supervision throughout the duration of the study.

## 10.2. PATIENT INFORMATION AND INFORMED CONSENT

Informed consent will be obtained before including the patient in the trial (Appendix III). The investigator is to inform the patient of the nature, duration and purpose of the study, as well as of all the obstacles and inconveniences which – within reason – may be expected from it. Furthermore, the patient is to receive information in writing. The participating patients must be legally competent to give informed consent, with the possibility of taking decisions at his/her own free will. The patient has the right to leave the study at any time.

## 10.3. CONFIDENTIALITY AND PATIENT PROTECTION

The processing of the data to be compiled by the study sponsor during the trial will be subject to current legislation as regards data protection. The patient will be identified in the records by the corresponding code number only. The patient is to be guaranteed anonymity, and is to be informed that all communication will take place between him/her and the investigator – not the sponsor of the trial.

# 11.- PRACTICAL ASPECTS

## 11.1. RESPONSABILITIES OF STUDY PARTICIPANTS

Obligations of the investigator

The investigators have to conduct the trial in accordance with the established design, and following all the indications of the present protocol or subsequent amendments.

Auxiliary staff

The auxiliary staff collaborating in the study has to follow the established norms and instructions of the investigators. They are also required to report any possible incidents to the investigators.

Norms for patients

The patients will be duly informed and instructed to adhere to the recommendations which make the study possible, as contemplated in this protocol.

## 11.2. PROTOCOL AMENDMENTS

Any changes, amendments or additions to the protocol will be signed by the sponsor and the principal investigator, and must be reported to the Clinical Research Ethics Committee and the Ministry of Health.

Any relevant protocol amendment will require a prior opinion from the Clinical Research Ethics Committee, and authorization from the Spanish Drug Agency.

## 11.3. DATA COLLECTION AND FILING

Data collection will be done directly in an electronic format. This will be carried out by the investigator and his/her collaborators, who will complete the database in accordance with the standard operative procedures (SOPs), in observation of the study protocol.

The information reflected in the database will be regarded as the primary data, with the exception of the patient filiations. The clinical history should also reflect patient participation in the trial, as well as the assigned code number and identification of the different visits taking place during the course of the study.

The data file will adapt to the SOPs of the sponsor procedures.

The subject identification list and written informed consent sheets will be filed separately in the file of the investigator, which will be filed in the same way in the corresponding site.

## 11.4. GOOD CLINICAL PRACTICE (GCP)

This clinical trial will comply with Good Clinical Practice (GCP).

The sponsor and sanitary authorities can audit and inspect the clinical study.

## 11.5 PUBLICATION

Publication of the results of the clinical trial will adhere to the specifications contained in article 38 of Royal Decree 223/2004.

## 11.6. STUDY DOCUMENTATION

1. Protocol.
2. APPENDIX I: CASE REPORT FORM (CRF) CONTENT
3. APPENDIX II: INVESTIGATOR’S BROCHURE
4. APPENDIX III: PATIENT INFORMATION AND WRITTEN INFORMED CONSENT
5. APPENDIX IV: INSURANCE
6. APPENDIX V: NOTIFICATION FORM OF SERIOUS ADVERSE EVENTS
7. APPENDIX VI: REFERENCES

# 12.- STATISTICAL ANALYSIS

The statistical analysis and data management is going to be realized by Lluita contra la SIDA Foundation. An informatized data base of the study is going to be created, it is going to be used to data management too. The statistical analysis is going to be carried out by the statistical programs *SPSS 15 and S-Plus.*

## 12.1. SAMPLE DESCRIPTION

A general descriptive analysis of all the variables of the study, overall and separately by groups of treatment is going to be done using mean, standard deviation, median, interquartile range, maximum and minimum values for the quantitative variables and absolute and relative frequencies of each category for categorical variables.

## 12.2. RESPONSE EVALUATION

The response evaluation is going to be done per-protocol, an interim analysis will be performed will be performed when 75% of subjects reach week 24 of follow-up , the final analysis will be based on patients completing the entire 48 weeks of treatment.

The statistical significance of the longitudinal changes in the HIV RNA viral load and lipid parameters are going to be assessed by the calculation of the slope of decay and compared using t-student, Wilcoxon or Mann-Whitney distinguishing between treatment groups and/or other relevant baseline factor.

HIV RNA viral load is going to be transformed by the log10 and if necessary, other transformations of the data are going to be considered.

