## 6.2. INCLUSION CRITERIA

1. Adult patient having a diagnosis of HIV-1 infection.
2. Antiretroviral therapy started at least 12 months before, always with a HAART combination including 2 NRTIs plus a PI
3. Current HAART combination including 2 NRTIs plus a PI.
4. Maintained undetectable plasma HIV-1 RNA (VL < 50 copies/mL) since the beginning of antiretroviral therapy, for at least 6 months.
5. Absence of suspected or documented resistance mutations in the RT associated to NNRTIs or to any NRTI.
6. Patient having at least one of the following conditions:

- Dyslipemia (LDL cholesterol >130 mg/dL or triglycerides > 350 mg/dL) derived from their current PI regimen or current use of lipid lowering agents due to dyslipemia,
- Antiretroviral-related gastrointestinal disturbances, or
- Low patient’s satisfaction associated with the current regimen posology (BID regimen, ritonavir use, ritonavir intolerance…).

1. Good treatment adherence.
2. Voluntary written informed consent.

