# 8.- TRIAL CONDUCTION AND RESPONSE EVALUATION

## 8.1. CRITERIA FOR RESPONSE EVALUATION

### 8.1.1. Principal Study Variable

Viral load at week 48.

Virologic failure is defined as an increase in HIV RNA >50 copies/mL in 2 determinations within 1 month. The first date with VL > 50 copies/mL will be used to calculate time to virologic failure.

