### 8.1.3. Endpoints

**Primary objective:**

To compare the virological efficacy of etravirine-based regimen with standard PI-containing regimens.

- The percentage of patients who experienced virologic failure throughout the 48 weeks of the study. Virologic failure will be defined as an increase in HIV RNA >50 copies in 2 determinations within 1 month.
- Time to virologic failure, defined as an increase in HIV RNA >50 copies in 2 determinations within 1 month. The first date with VL > 50 will be used to calculate time to virologic failure.
- Determination of antiretroviral resistance at the time of virological failure and comparison with baseline.

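### The only stated between-group test of virological response compares the slope of decay of HIV RNA in patients already below 50 copies/mL, and so does not measure the primary endpoints

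*Protocol*

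**What the plan says.** **Population.** Protocol 6.2 requires "Maintained undetectable plasma HIV-1 RNA (VL < 50 copies/mL) since the beginning of antiretroviral therapy, for at least 6 months".

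**Endpoints for the primary objective.** Section 8.1.3 lists "The percentage of patients who experienced virologic failure throughout the 48 weeks of the study", then "Time to virologic failure, defined as an increase in HIV RNA >50 copies in 2 determinations within 1 month", and resistance at failure. Section 8.1.1 names the principal variable as "Viral load at week 48" and goes straight on to define virologic failure and how its date is set. Section 1.14 says only viral load.

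**Comparative analysis.** Section 12.2 states that "longitudinal changes in the HIV RNA viral load and lipid parameters are going to be assessed by the calculation of the slope of decay" and that these are "compared using t-student, Wilcoxon or Mann-Whitney distinguishing between treatment groups and/or other relevant baseline factor". It adds that "HIV RNA viral load is going to be transformed by the log10" and that "the final analysis will be based on patients completing the entire 48 weeks of treatment".

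**Other uses of failure data.** Section 12.1 promises descriptive frequencies by arm for categorical variables. Section 6.5 compares failure rates between arms at the interim evaluation.

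**The concern.** A slope of decay suits patients who start with measurable viraemia and are expected to fall. This trial starts from suppression, and the question is who rebounds and when. The method fixed for HIV RNA therefore describes a quantity that the recorded data can hardly contain, and it is not linked to the endpoints in 8.1.3.

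At stake is whether the final comparison answers the primary objective. Section 12.4 wants the pilot to inform the design of adequately powered trials. A failure proportion with its uncertainty does that; a mean difference in log10 slope does not.

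**Working it through.** **Inputs.** Visits at weeks 0, 4, 12, 24, 36 and 48 (8.3); entry below 50 copies/mL (6.2); log10 scale (12.2); 20 patients per arm (12.4). The protocol gives no alpha, power, margin or expected failure rate, so there is no planned figure to reproduce. The viral load profiles below are assumptions. Values below 50 are set to 50, because 12.2 gives no rule for them.

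**Formula.** Least-squares slope b = Σ(t − t̄)(y − log10 50) / Σ(t − t̄)², with t̄ = 124/6 = 20.67 weeks and Σ(t − t̄)² = 1773.3. (Subtracting a constant from y leaves the slope unchanged.) The visit weights t − t̄ are −20.67, −16.67, −8.67, +3.33, +15.33 and +27.33.

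**1. Suppressed patient.** Every y − log10 50 is 0, so b = 0.

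**2. Same rebound, different timing.** Values of 500 (1.000 log10 above 50) then 2,000 (1.602 above), re-suppressed afterwards:

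| Visits above 50 | Numerator | Slope (log10/week) |
|---|---|---|
| 24 and 36 | 3.33×1.000 + 15.33×1.602 = 27.90 | +0.0157 |
| 12 and 24 | −8.67×1.000 + 3.33×1.602 = −3.33 | −0.0019 |
| 4 and 12 | −16.67×1.000 − 8.67×1.602 = −30.55 | −0.0172 |

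Each patient is above 50 on two consecutive visits, which is failure in the wording of 6.6. Two of the three show an apparent decay.

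**3. Effect of stopping at failure.** If the week 4 and 12 patient contributes only weeks 0, 4 and 12, then t̄ = 5.33, Σ(t − t̄)² = 74.67 and b = (−1.33×1.000 + 6.67×1.602)/74.67 = +0.1252. The same failure gives −0.0172 or +0.1252, depending on whether later values are used.

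**4. Size of rebound against number of failures.** Assume rebounds at weeks 36 and 48 (summed weight 42.67). Four of 20 etravirine patients are at 200 copies/mL (+0.602) and one of 20 controls is at 100,000 (+3.301).
- Mean rise: 4×0.602/20 = 0.120 against 3.301/20 = 0.165.
- Mean slope: 0.120×42.67/1773.3 = +0.0029 against 0.165×42.67/1773.3 = +0.0040.
- The difference in means goes against control, although failures are 4 against 1 against etravirine. The t-test gives t = −0.26, p = 0.80.
- Mean ranks: etravirine (16×18 + 4×37.5)/20 = 21.9; control (19×18 + 40)/20 = 19.1. Mann-Whitney p = 0.19, in the direction of the failure counts.

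Section 12.2 leaves the choice of test open, so the direction of the result can depend on that choice.

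**5. What a direct comparison would give.** For 4/20 against 1/20 the difference is 15 percentage points. The Wilson limits are 8.1% to 41.6% and 0.9% to 23.6%. The Newcombe 95% interval is 0.15 − √(0.119² + 0.186²) to 0.15 + √(0.216² + 0.041²), about −7 to +37 points (Fisher p = 0.34). With 0/20 failures the exact upper limit is 1 − 0.025^(1/20) = 16.8%.

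**The case against.** The strongest reply is that this is an exploratory pilot, that a statistical analysis plan may exist, and that tests for proportions and survival methods are commonly left to it. That is right as far as it goes: the absence of such tests is not the finding. The finding is that the protocol itself names a method for HIV RNA that does not fit its own population and endpoints, and an analysis plan would have to contradict 12.2 to repair it.

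A reader might infer several stronger points that the documents do not support.

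- **That failure percentages are never analysed.** Section 12.1 gives frequencies by arm, and 6.5 uses failure rates at the interim. What is missing is their use as the stated basis of the final comparison.
- **That the slope test will point the wrong way.** The reversal in step 4 is a difference in means with p = 0.80, on assumed values. A rank test on the same data does not reverse.
- **That the slope test has no power.** In simulation with assumed failure of 30% against 5%, Mann-Whitney on slopes rejected in 0% of runs among completers, but in about 57% when failures were kept with data up to failure. The zero comes from the completers-only set, because 6.6 ends participation at virologic failure. It is an adjoining defect of 12.2, not proof against slopes. Applied literally, that set would also drop the confirmed failures in steps 2 to 4.
- **That viral load cannot fall at all.** Viraemia below 50 could change, and the assay limit is not given. The statement holds for values recorded at the 50-copy cut-off.
- **That the protocol has contradictory primary endpoints.** Section 8.1.1 continues with the definition of virologic failure, so the difference from 8.1.3 is loose wording.

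The objection also does not extend to lipids, where a fall is the hypothesis (4.1).

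**Conclusion.** The point holds as a mismatch between a stated method and the stated endpoints. At the 50-copy cut-off a suppressed patient's slope is 0. The slope of a patient who rebounds reflects the timing and height of the rebound and the handling of later values, not whether or when failure occurred. In the assumed profiles one pattern of failure ranges from −0.0172 to +0.0157 log10/week by timing alone.

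This rests on least-squares slopes at the scheduled visits, values below 50 set to 50, and illustrative viral loads. The profiles meet the consecutive-visit definition in 6.6; the one-month window in 8.1.3 would need an extra sample between scheduled visits. The conclusion about fit does not depend on these values: a slope is neither a proportion nor a time to event. Because the sentence governs the primary objective it should be corrected, but no confirmatory claim, alpha or margin rests on it.

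**What to change.** - In 12.2, remove HIV RNA from the slope sentence; lipids may stay.
- State the primary comparison: the difference (etravirine minus control) in the proportion with virologic failure by week 48, with a two-sided 95% confidence interval suited to small samples (Newcombe or exact).
- Give Kaplan-Meier estimates by arm for time to virologic failure.
- Count patients withdrawn for virologic failure as failures, so that the completers-only wording in 12.2 does not remove them.
- Align the wording of 1.14 and 8.1.1 with 8.1.3.

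The cost is protocol or analysis-plan wording only, with no new data or visits. The estimate will be imprecise at 20 per arm: two-sided Fisher significance at 0.05 needs at least 5/20 against 0/20, and power is about 17% for assumed failure of 20% against 5%. Estimation with an interval suits a pilot, and the interval shows that imprecision openly.

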***Hypothesis***

- Hypothesis 1. Switching from a PI to etravirine, as a simplification strategy, in subjects with maintained viral suppression will be associated with comparable rates of virological suppression.
- Hypothesis 2. Switching to etravirine in this clinical context will be associated with an improvement of lipid parameters and patient’s satisfaction in comparison with remaining on the previous PI-based regimen.

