**Secondary objectives:**

To compare the immunological efficacy of etravirine-based regimen with standard PI-containing regimens.

- Changes in CD4+/CD8+ T lymphocytes at week 48 from baseline.

To compare the tolerability and toxicity of etravirine-based regimen with standard PI-containing regimens.

- Changes in lipid parameters (total, HDL-, LDL-cholesterol and triglyceride levels) at week 48 relative to baseline values.
- Changes in the administration of lipid-lowering drugs throughout the study (new administrations or the withdrawal of previous lipid-lowering drugs).
- Percentage of patients who withdraw from the study.
- Percentage of patients who withdraw from the study due to toxicity.
- Percentage of patients with toxicity ≥ grade 3.

To compare the cardiovascular risk of etravirine-based regimen with standard PI-containing regimens.

- Changes in cardiovascular risk estimated by changes in the SCORE equation at week 48 relative to baseline values.

To compare patient’s satisfaction of etravirine-based regimen with standard PI-containing regimens.

- Changes in patient’s satisfaction at week 48 from baseline, using a 100 mm analogue visual scale.

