## 8.3. TRIAL DEVELOPMENT

After accepting the participation, patients would be assessed the first visit. Study visits would be at entry (BL) and weeks 4, 12, 24, 36 and 48.

Plasma samples will be stored at –80ºC.

Viral load, complete blood count, CD4 cells count, and a complete biochemistry and haematology will be performed at every visit (except for week 4 where only CD4 count and viral load will be performed).

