**Flow chart of study procedures:**

|  | SCR | BL | Wk 4 | Wk 12 | Wk 24 | Wk 36 | Wk 48 |
| --- | --- | --- | --- | --- | --- | --- | --- |
| Informed consent |  |  |  |  |  |  |  |
| Pregnancy test |  |  |  |  |  |  |  |
| Clinical visit |  |  |  |  |  |  |  |
| HIV1-1 Viral load |  a |  |  |  |  |  |  |
| CD4 cell count |  a |  |  |  |  |  |  |
| Biochemistry (including lipid profile) |  a |  |  |  |  |  |  |
| Haematology |  a |  |  |  |  |  |  |
| Patient’s satisfaction |  |  |  |  |  |  |  |
| SCORE equation (blood pressure) |  |  |  |  |  |  |  |
| Adverse events |  |  |  |  |  |  |  |
| Plasma sample storageb |  |  |  |  |  |  |  |

a A blood test including HIV-1 RNA, CD4+ counts, biochemistry and haematology performed within 3 months previous to the baseline visit will be accepted as screening.

b Genotypic resistance testing will be performed to all participants experiencing virologic failure during the study.

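### The lipid endpoint is change from baseline at week 48, but section 12.2 tests an unadjusted slope, which equals that change only if lipids move in a straight line

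*Protocol*

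**What the plan says.** Three places in the protocol bear on the lipid comparison.

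- **Hypothesis 2 (section 4.1)** expects the switch to be "associated with an improvement of lipid parameters and patient’s satisfaction in comparison with remaining on the previous PI-based regimen".
- **Section 8.1.3, secondary endpoints**, defines the outcome as "Changes in lipid parameters (total, HDL-, LDL-cholesterol and triglyceride levels) at week 48 relative to baseline values".
- **Section 12.2** fixes the analysis: "lipid parameters are going to be assessed by the calculation of the slope of decay and compared using t-student, Wilcoxon or Mann-Whitney". The sentence continues with "distinguishing between treatment groups and/or other relevant baseline factor". That allows results to be split by a baseline factor, but it is not covariate adjustment for the baseline lipid value.

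On timing, section 8.3 states: "Study visits would be at entry (BL) and weeks 4, 12, 24, 36 and 48". It adds that "a complete biochemistry and haematology will be performed at every visit (except for week 4", where only CD4 count and viral load are done. The flow chart places the lipid profile within biochemistry. Lipids are therefore available at weeks 0, 12, 24, 36 and 48.

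**The concern.** Sections 8.1.3 and 12.2 attach two different quantities to the same outcome. One is the difference between two time points; the other is a rate of change over all visits. They agree only if lipids change at a constant rate for 48 weeks. The intervention is a change of drug made once, at randomisation, and nothing in the protocol says that the lipid response would be linear.

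The baseline lipid value is collected but not used as a covariate. Baseline lipids are likely to vary widely, because high lipids are only one of three alternative entry conditions in section 6.2. Allocation of 20 per arm is unstratified (section 5.3).

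At stake is how the lipid half of Hypothesis 2 is estimated, and what the pilot passes on. Section 12.4 says that the trial should inform the design of later, adequately powered trials. If slope × 48 weeks returned 80% of the true week-48 difference and were used as the planning effect, with the SD unchanged, the next trial would be sized at 1/0.80² = 1.56 times what it needs.

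**Working it through.** The protocol gives no lipid SD, effect size, correlation, alpha or power, so there is no stated figure to reproduce. The check compares the planned estimator with the stated endpoint, and then compares precision.

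**Inputs from the protocol.** Lipid times 0, 12, 24, 36 and 48 weeks (section 8.3 and flow chart); 20 patients per arm (section 12.4).

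**Assumptions.** The slope is an ordinary least-squares slope per patient, which is the natural reading when slopes are compared by a t or rank test. The SD is 1 at each visit. The correlation rho between any two visits is equal (compound symmetry), with rho from 0.5 to 0.8. The time course is either a step complete by week 12 or a straight line.

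**Step 1: what the slope estimates.** The centred times are −24, −12, 0, 12, 24, and their squares sum to 1440. The weights for slope × 48 are 48 × (centred time)/1440, that is −0.8, −0.4, 0, 0.4, 0.8.

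- Step course (0, 1, 1, 1, 1): −0.4 + 0 + 0.4 + 0.8 = **0.80** of the week-48 change.
- Linear course (0, 0.25, 0.5, 0.75, 1): −0.1 + 0 + 0.3 + 0.8 = **1.00**.

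This result does not depend on rho.

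**Step 2: variance per patient.**

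- ANCOVA at week 48: 1 − rho².
- Unadjusted change score: 2(1 − rho).
- Slope × 48: the squared weights sum to 0.64 + 0.16 + 0 + 0.16 + 0.64 = 1.6 and the weights sum to zero, so the variance is 1.6(1 − rho).

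**Step 3: information of ANCOVA relative to each alternative** (signal²/variance).

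| Comparison | Formula | rho 0.5 | rho 0.8 |
| --- | --- | --- | --- |
| vs change score | 2/(1 + rho) | 1.33 | 1.11 |
| vs slope, step | (1.6/0.64)/(1 + rho) = 2.5/(1 + rho) | 1.67 | 1.39 |
| vs slope, linear | 1.6/(1 + rho) | 1.07 | 0.89 |

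For a linear course the two break even at rho = 0.6.

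**Step 4: simulation.** 4,000 trials per scenario, 20 per arm, assumed effect 0.8 SD, two-sided 5%. The table shows power.

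| Scenario | Slope | Change score | ANCOVA |
| --- | --- | --- | --- |
| rho 0.5, step | 61% | 69% | 80% |
| rho 0.5, linear | 80% | 70% | 80% |
| rho 0.8, step | 93% | 97% | 98% |
| rho 0.8, linear | 99% | 97% | 98% |

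With no true effect, all three methods rejected in about 5% of trials.

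**Step 5: sensitivity.** The analytic comparison with the slope was repeated over 36 scenarios: rho 0.3 to 0.8; compound symmetry or AR(1); step, gradual or linear course. ANCOVA was better in 32, tied in 1, and worse by 4% to 11% in 3. All three losses are under compound symmetry at rho 0.7 or 0.8, with a linear or gradual course. Under AR(1), ANCOVA was ahead in every scenario, by a factor of 1.16 to 2.52.

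**The case against.** The strongest reply is that the slope is a legitimate summary. It uses all five lipid measurements, while ANCOVA of the week-48 value leaves out the three intermediate ones. It holds its type I error. If lipids do change linearly and visits are highly correlated, it is slightly more efficient. The early step is an assumption that the protocol neither states nor excludes. These are also secondary outcomes of a 40-patient pilot. All of this stands. It limits the precision argument, but it does not remove the mismatch between the endpoint and the test. A repeated-measures model with a week-48 contrast also answers the complaint about discarded visits.

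A reader might infer more than the documents support:

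- **That ANCOVA is always more precise than the slope.** This holds only against the unadjusted change score. Against the slope it depends on a time course and a correlation that the protocol does not give.
- **That selection on high lipids biases the comparison through regression to the mean.** Entry precedes randomisation, so the effect falls on both arms alike. It distorts within-arm changes, not the between-arm contrast.
- **That chance imbalance is a large threat.** The baseline difference has a standard error of √(2/20) = 0.32 SD, but only −0.8(1 − rho) of it carries into slope × 48. In size that is 0.13 SD at rho 0.5 and 0.05 SD at rho 0.8.
- **That averaging the on-treatment visits would gain still more.** Such an average is not the week-48 change that section 8.1.3 defines.
- **That CD4, SCORE and satisfaction share the fault.** Section 12.2 assigns no slope to them, and their analysis may be left to the SAP.

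**Conclusion.** The point holds in a limited form. The method fixed in section 12.2 does not estimate the endpoint defined in section 8.1.3 unless lipids move linearly. If the effect is complete by week 12 and persists, slope × 48 weeks gives 80% of the week-48 change. The baseline lipid value is collected but not adjusted for.

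Under compound symmetry with rho 0.5 to 0.8, ANCOVA carries 33% to 11% more information than the unadjusted change score. It carries 1.67 to 1.39 times the information of the slope for an early step. For a linear course it ranges from a 7% gain to an 11% loss against the slope. The time courses and correlations are assumptions; the measurement times and the endpoint definition are the protocol's.

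The planned test is not invalid, and the documents do not show that Hypothesis 2 would be missed because of it, since no lipid effect size, SD or power is stated. The case for change rests on matching the analysis to the endpoint at almost no cost, with a likely but not certain gain in precision.

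**What to change.** Amend section 12.2 so that each lipid parameter is analysed in one of two ways:

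- ANCOVA of the week-48 value (log scale if skewed) on treatment arm and the baseline value of the same lipid; or
- a repeated-measures model over weeks 12 to 48, adjusted for the baseline value, with the week-48 between-arm contrast named as the result.

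Report the between-arm difference with a 95% confidence interval, and keep the slope comparison as supportive.

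The cost is a change of wording in section 12.2. No new visits or measurements are needed. The final analysis is restricted to patients who complete 48 weeks, so week-48 values should be nearly complete. The downside is the possible small loss against the slope (up to 11% in the cases examined) if the course is linear or nearly so and visits are highly correlated.

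This change does not resolve the restriction to completers, or lipid-lowering drugs started or stopped during follow-up. Both affect the lipid comparison under either method.
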